## Abstract

**Introduction:**

Hyperlipidemia serves as a significant risk factor for cardiovascular diseases and cognitive impairment, making early intervention and management highly necessary. Infrared moxibustion, a modern complementary and alternative therapy, currently lacks high-quality clinical research to substantiate its efficacy and underlying mechanisms. Therefore, this study aims to evaluate the effects of infrared moxibustion on blood lipid levels in patients with hyperlipidemia, and to explore its potential mechanisms by analyzing changes in gut microbiota and their metabolites, as well as alterations in brain gray matter volume.

**Patient and methods:**

This study will recruit 158 patients with mild hyperlipidemia and randomly assign them to either a genuine infrared moxibustion group or a sham infrared moxibustion group. The intervention will be administered twice weekly for a total of 8 weeks. Blood lipid levels, Montreal Cognitive Assessment scores, Hamilton Depression Rating Scale scores, Hamilton Anxiety Scale scores, and Pittsburgh Sleep Quality Index scores will be compared between the two groups before treatment, and at 4, 8, and 12 weeks post-treatment. Additionally, changes in gut microbiota, the gut microbiota metabolite trimethylamine N-oxide (TMAO), and brain gray matter volume will be detected and compared between the two groups before treatment and at 8 weeks post-treatment (See Graphic Abstract).

## Introduction

1.

Hyperlipidemia (HLP) refers to a systemic lipid metabolism abnormality characterized by elevated levels of total cholesterol (TC), triglycerides (TG), and/or low-density lipoprotein cholesterol (LDL-C), and/or reduced levels of high-density lipoprotein cholesterol (HDL-C) in the plasma due to various causes. HLP, particularly elevated LDL-C levels, has been established as a risk factor for cardiovascular diseases and cognitive disorders (CD) [1,2]. While its role in the former has been extensively studied, its contribution to the latter remains to be explored. It has been reported that alterations in plasma lipid profiles appear to exacerbate cognitive decline, thereby increasing the risk of developing Alzheimer’s disease in non-demented elderly individuals [3–6]. This could be attributed to the fact that dyslipidemia negatively impacts hippocampal synaptic plasticity by promoting the accumulation of Aβ and TRPM2 [7,8], activating microglia, exerts a detrimental impact on hippocampal synaptic plasticity [9], facilitates hippocampal atrophy [10–12], mediates large-scale brain network abnormalities [13], and ultimately intensifies cognitive decline. Cognitive decline weakens individuals’ abilities in memory, thinking, comprehension, coordination, communication, and more. Early intervention targeting HLP may reduce the risk of developing CD [14]. Therefore, in-depth research into the underlying pathogenesis and effective therapeutic approaches for HLP holds crucial significance for improving the prevention and treatment of CD.

Currently, statins serve as the mainstream drugs for clinical treatment of hyperlipidemia, with proven lipid-lowering efficacy. Although some early studies have reported a potential association between statins and cognitive decline [15], current evidence-based research generally indicates that these drugs have a neutral effect on cognition and may even confer a protective effect. However, in clinical practice, some patients experience varying degrees of drug intolerance, such as muscle side effects [16,17], and low medication adherence [18]. Furthermore, despite the active recommendation of lifestyle interventions by clinical guidelines, the actual implementation and persistence among patients in real-world clinical settings remain unsatisfactory. Therefore, this highlights the urgent clinical need to explore effective and safe complementary or alternative therapies.

Notably, moxibustion is utilized in clinical practice as an adjunctive treatment for HLP. Preliminary clinical studies and systematic reviews suggest that moxibustion may offer potential benefits in regulating blood lipids [19–21]. However, the overall quality of existing research is generally suboptimal, with issues such as small sample sizes, inconsistent methodological quality and the absence of a double-blind design. Furthermore, traditional moxibustion is fraught with limitations, including smoke irritation from moxa and challenges in precisely controlling temperature. In contrast, infrared moxibustion (IM), a modern and innovative moxibustion technique, integrates the dual therapeutic effects of infrared radiation and moxibustion without the associated smoke irritation. Nevertheless, the current evidence supporting the use of IM for the treatment of hyperlipidemia is relatively weak, and its therapeutic mechanisms remain to be further explored.

An increasing number of scholars have proposed correlations between gut microbiota and their metabolites with HLP. Dysbiosis of the gut microbiota may serve as a mediating factor in the causal relationship between a high-calorie diet and CD [22]. Xia M et al. revealed that, compared to healthy volunteers, the mixed fecal samples from elderly HLP patients were predominantly composed of *Firmicutes* and *Proteobacteria*, with an increased relative abundance of *Helicobacter, Lactobacillus*, and *Desulfovibrio*, and a decreased relative abundance of *Parabacteroides, Bacteroides, Blautia, Bifidobacterium*, and *Peptococcus* [23]. Among the metabolites produced by the gut microbiota, trimethylamine-N-oxide (TMAO) has garnered considerable attention for its involvement in the regulation of lipid metabolism and inflammatory responses, and is recognized as a risk factor for HLP [24]. Numerous animal experiments and clinical studies have demonstrated that a high-fat diet increases TMAO production [25–27]. Fei’erdun T et al. discovered that HLP patients exhibited higher plasma levels of TMAO compared to those with normal lipid profiles, with its concentration showing a positive correlation with TG and a negative correlation with high-density lipoprotein cholesterol HDL-C [27]. A high-fat diet may trigger or exacerbate the onset of cognitive impairment by increasing the abundance of harmful bacterial genera and TMAO levels, while simultaneously reducing the abundance of beneficial bacterial genera [28]. Our previous research indicated that TMAO is involved in the pathogenesis of mild cognitive impairment (MCI) and can serve as a biomarker and therapeutic target for MCI [29]. Furthermore, TMAO and its precursor substances have been confirmed by multiple studies to be associated with brain volume changes, cognitive decline, and an increased risk of dementia [30–32]. Yaqub A and colleagues proposed that elevated levels of TMAO-related metabolites may induce brain atrophy, thereby increasing the risk of dementia [30]. Existing evidence shows that traditional moxibustion can reduce the levels of TMAO in animals fed a high-fat diet and improve their lipid profiles. Moreover, changes in its precursor substances exhibit a significant correlation with specific bacterial groups [33,34]. Moreover, a study has observed that acupuncture intervention can induce alterations in brain structure in obese patients and animals on a high-fat diet [35], suggesting that acupuncture and moxibustion therapies may participate in metabolic regulation by influencing the central nervous system.

Therefore, we designed this randomized, double-blind clinical study. We hypothesize that infrared moxibustion may decrease blood lipid levels in patients with mild hyperlipidemia. The underlying mechanisms may be associated with the modulation of intestinal microbiota abundance, the reduction of TMAO levels, and the mitigation of cerebral atrophy. This study holds significant importance in reducing the risk of CD in HLP patients, serving as an early preventive measure. Furthermore, the findings of this study can offer a novel non-pharmacological therapeutic option for the clinical management of HLP, possessing substantial scientific value and broad clinical application prospects.

## Patients and methods

2.

### Study design

2.1.

This study will conduct a prospective, multicenter, double-blind randomized controlled trial at the Second Affiliated Hospital of Hunan University of Chinese Medicine, Hunan Integrated Traditional Chinese and Western Medicine Hospital, and Chenzhou First People’s Hospital. The study has received approval from the Ethics Committee of the Second Affiliated Hospital of Hunan University of Chinese Medicine (Approval Certificate Numbers: KY-2025-023-01, [2025] No. 371, (Research) No. 2025100), and has been registered on the International Traditional Medicine Clinical Trial Registry Platform (https://itmctr.ccebtcm.org.cn/mgt/search; Registration Number: ITMCTR2025001463). This study will be reported in accordance with the Declaration of Helsinki and the Standard Protocol Items: Recommendations for Interventional Trials (SPIRIT) guidelines. We plan to recruit 158 eligible participants from August 2025 to June 2027. After signing informed consent forms, they will be randomly assigned to two groups: the infrared moxibustion group (IM group) and the sham infrared moxibustion group (Sham IM group), as detailed in Figure 1.

**Figure 1. F0001:**
[figure not shown]
Flow diagram.

### Randomization, allocation concealment, and blinding

2.2.

Central stratified randomization will be employed using SAS 9.3 (SAS Institute Inc., Cary, NC, USA) statistical software to generate random numbers. Eligible participants will be randomly assigned to the IM group and the sham IM group in a 1:1 ratio through a central randomization system. The central randomization system will be managed by independent personnel who will not be involved in participant recruitment, intervention delivery, outcome assessment, or statistical analysis to prevent selection bias. Both participants and the treating physicians will be blinded to the treatment allocation between active infrared moxibustion and sham infrared moxibustion. Throughout the data collection and analysis process, assessors and statisticians will also be blinded to the treatment allocation.

### Participants

2.3.

#### Diagnosis criteria

2.3.1.

Participants must meet the diagnostic criteria for mild hyperlipidemia [36]. Mild hyperlipidemia can be diagnosed if patients meet one or more of the following fasting venous plasma test indicators: (1) 2.3 mmol/L > TG ≥ 1.7 mmol/L; (2) 6.2 mmol/L > TC ≥ 5.2 mmol/L; (3) 4.1 mmol/L > LDL-*C* ≥ 3.4 mmol/L.

#### Inclusion criteria

2.3.2.

(1) Meet the diagnostic criteria for hyperlipidemia; (2) Aged between 18 and 70 years; (3) Not currently using lipid-lowering medications, or have discontinued lipid-lowering medications for at least one month, and are not participating in other clinical studies; (4) Sign an informed consent form.

#### Exclusion criteria

2.3.3.

(1) Secondary hyperlipidemia caused by other diseases (e.g. nephrotic syndrome, gout, hypothyroidism, acute or chronic hepatobiliary diseases, diabetes); (2) Concomitant severe primary diseases of the liver, heart, or brain; (3) Allergic to infrared therapy; (4) Have undergone gallbladder surgery or major gastrointestinal surgery within the past six months; (5) Pregnant or lactating women; (6) Poor compliance.

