#### IM group

2.4.1.

Participants in the observation group will receive infrared moxibustion intervention using an infrared moxibustion chamber (Model CH-6, Hunan Cihui Medical Technology Co., Ltd., Changsha, Hunan). Participants will lie supine with their entire body below the head and neck placed inside the infrared chamber. Infrared moxibustion will be initiated with a single button press. The temperature inside the chamber will be set to 50 °C, with a treatment duration of 40 min, once per day, twice per week, for a total of 8 weeks.

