#### Sham IM group

2.4.2.

Participants in the control group will receive sham far-infrared moxibustion intervention. The treatment protocol will be identical to that of the treatment group, except that the device will not emit infrared rays when turned on.

In addition, both groups of participants will receive therapeutic lifestyle changes, including a balanced diet, moderate increase in physical activity, weight control, smoking cessation, and limited alcohol consumption.

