The gut microbiota composition of patients with HLP differs significantly from that of healthy individuals [42]. Previous studies have demonstrated that moxibustion can modulate gut microbiota diversity in animal models or patients with hyperlipidemia, downregulating the abundance of TMA-producing bacterial groups (such as *Lachnospiraceae_NK4A136*, *Firmicutes*), and upregulating TMA-degrading bacteria (such as *Akkermansia*, *Enterococcus*, and *un_f_Muribaculaceae*) [34,43,44]. Gut microbiota-derived TMAO and its precursors are key metabolites mediating dyslipidemia [27,45], changes in brain volume [30], and cognitive impairmen [31]. Animal studies have further validated their role through fecal microbiota transplantation [46,47] and TMAO inhibitors [48,49]. An animal study showed that compared to normally fed rats, long-term high-fat diet-fed rats exhibit elevated blood lipids, impaired learning and memory, increased plasma and hippocampal TMAO levels, along with reduced glucose uptake capacity and volume in hippocampal tissue [50]. In clinical studies, serum triglyceride levels significantly differ between patients with cognitive impairment and those with normal cognition, with this difference significantly associated with reduced entorhinal cortex and hippocampal volumes [51]. A cross-sectional study by Chen Y et al. demonstrated a close correlation between TMAO, its precursor choline, and white matter hyperintensity volume [32]. Further a clinical cohort study found that plasma choline, a TMAO precursor, is significantly associated with reduced cognitive function, decreased total brain volume, and increased white matter hyperintensity volume, while carnitine is associated with reduced white matter hyperintensity volume [30]. Research by Gordon, S., et al. also suggests that TMAO levels in Puerto Rican adults may have a negative correlation with brain aging and hippocampal volume [52].

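### The entry criteria wash out lipid-lowering drugs but not current or recent moxibustion, acupuncture or infrared/heat therapy, so users of the treatment class under test can be enrolled and allocated to sham

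*Protocol article*

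**What the plan says.** Section 2.3.2 of the protocol article deals with earlier treatment in one item: "Not currently using lipid-lowering medications, or have discontinued lipid-lowering medications for at least one month, and are not participating in other clinical studies". Section 2.3.3 then lists six exclusions. The first two cover secondary hyperlipidemia and severe organ disease. The next two read "3) Allergic to infrared therapy; (4) Have undergone gallbladder surgery or major gastrointestinal surgery within the past six months". The last two concern pregnancy or breastfeeding, and compliance.

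Sections 2.4.1 and 2.4.2 describe the two arms and add lifestyle advice for both. They set no rule on other non-drug therapies during the trial.

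Elsewhere the article treats this class of therapy as biologically active in the target disease. The Introduction says that "moxibustion is utilized in clinical practice as an adjunctive treatment for HLP" and that it may benefit blood lipids. The Discussion says that "moxibustion can modulate gut microbiota diversity in animal models or patients with hyperlipidemia". It also cites animal work in which moxibustion lowered TMAO and improved lipids, and studies in which acupuncture improved lipids in obese patients.

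For the active arm, "The temperature inside the chamber will be set to 50 °C, with a treatment duration of 40 min". The sham session is the same "except that the device will not emit infrared rays when turned on". Section 2.2 states that participants are blinded.

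**The concern.** The plan considered earlier lipid treatment but covered only drugs. Applied as printed, the criteria admit a patient who is having regular moxibustion or infrared sessions, and that patient has an even chance of allocation to sham.

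Two things are at stake:

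- **Contrast.** On the article's own premises, outside therapy of this class could move the primary endpoint (change in LDL-C to week 8, section 2.5.1) and two mechanistic endpoints, TMAO and the gut microbiota. Sham patients who receive it during the trial, or whose response to it carries over, would look more like actively treated patients. Active patients would have less left to gain. Both push the estimate towards no difference.
- **Blinding.** A patient who has used an infrared chamber knows what a live session feels like, and may notice a session without infrared output.

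**Working it through.** **1. Is the gap in the text?** The places where a restriction could stand, side by side:

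| Place | What it restricts | Moxibustion, acupuncture or heat therapy? |
|---|---|---|
| 2.3.2 Inclusion | Lipid-lowering drugs (one month), other clinical studies | No |
| 2.3.3 Exclusion | Secondary disease, severe disease, infrared allergy, recent surgery, pregnancy or lactation, poor compliance | Allergy only, not use |
| 2.4.1 and 2.4.2 Interventions | Nothing on outside therapy | No |

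The gap is confirmed.

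**2. The plan's own sample size.** Section 2.7 gives LDL-C of 4.41 (SD 0.52) and 3.72 (SD 0.43) mmol/L, two-sided alpha 0.05, power 0.95, and 66 per group.

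- Difference: 4.41 − 3.72 = 0.69
- Pooled SD: √[(0.52² + 0.43²)/2] = 0.477
- d = 0.69/0.477 = 1.446
- n per group at power 0.95: 13 (normal approximation) or 14 (two-sample t-test)

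The stated 66 is not reproduced. Solving the t-test for n = 66 and power 0.95 gives d = 0.632. This discrepancy is a separate matter, but it means that the effect of dilution has to be shown under both values of d.

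**3. Dilution.** Assumption, not in the documents: a share p of patients, equal in both arms, contributes no active-versus-sham difference. The effect becomes d × (1 − p). Power comes from the noncentral t distribution with 66 per group (130 degrees of freedom).

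| p (assumed) | d implied by n = 66 | Power | d from printed means | Power |
|---|---|---|---|---|
| 0% | 0.632 | 95% | 1.446 | >99% |
| 5% | 0.601 | 93% | 1.374 | >99% |
| 10% | 0.569 | 90% | 1.302 | >99% |
| 20% | 0.506 | 82% | 1.157 | >99% |
| 30% | 0.443 | 71% | 1.012 | >99% |

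In both columns the expected estimate shrinks by the factor (1 − p), whatever happens to power.

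**4. When does dilution arise?** The endpoint is change from baseline. The effect of stable use that began well before baseline is already in the baseline LDL-C and need not produce further change in the sham arm. Contrast is lost in three situations: use starts during the trial, an earlier course carries over into the 8 weeks, or outside use and trial treatment do not add up, so that users in the active arm gain less.

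**The case against.** Several objections have force.

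- **Frequency.** A reader might infer from the Introduction that moxibustion is routine for hyperlipidemia, so that contamination is certain. The text says only that it is used as an adjunct and gives no rate. It presents infrared moxibustion as a modern technique with weak evidence. The Discussion names diet and lifestyle as the main interventions in mild disease. This stands: how common exposure is cannot be read from the article.
- **Mechanism.** Stable earlier use is absorbed into baseline, and entry requires at least one currently abnormal lipid value. Randomisation should balance earlier users between arms, so a systematic baseline bias is not the expected result. This also stands. Dilution is conditional, and its expected direction is towards no difference.
- **Power.** The lower figures rest on an assumed p and a back-solved d. Under the printed means, power is hardly affected. This stands, although those means do not lead to the planned 66, so they reassure only in part.
- **Blinding.** A reader might infer that excluding experienced patients would secure the blind. The article does not say whether the sham chamber is warmed. If it is not, patients new to the therapy could notice too. Earlier acupuncture or traditional moxibustion also tells a patient little about a whole-body infrared chamber. The recognition argument is therefore limited to those who know chamber therapy.
- **Condensed article.** Rules on concurrent therapy may stand in a full protocol that is not shown. That is fair for conduct during the trial. It is weaker for entry, because the eligibility lists are printed as numbered criteria and include a washout for drugs.

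**Conclusion.** The concern holds in a limited form. The printed criteria let in current and recent users of the treatment class under test, and some can be allocated to sham. This may shrink the LDL-C, TMAO and microbiota contrasts if use is concurrent, carries over or does not add to trial treatment. It may also help patients familiar with infrared chambers to recognise the sham.

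The size is unknown. Over an assumed 5% to 30% of patients contributing no contrast, power at 66 per group runs from 93% down to 71% if the true effect is the one that 66 implies, and stays above 99% if it is the one printed in section 2.7. The documents do not show that dilution or unblinding will occur, nor that outside use is common. The case for a change rests on its low cost.

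**What to change.** - Add to section 2.3.3 an exclusion for current use, or use within an interval before baseline that the sponsor fixes, of moxibustion (traditional or infrared), acupuncture, or infrared/heat therapy.
- Ask participants not to start any of these outside the trial before the week-12 visit.
- Record earlier lifetime exposure at T1 as a baseline variable, and repeat the primary LDL-C comparison in exposure-naive patients as a sensitivity analysis.

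**Cost:** one eligibility line, one instruction to participants and one case report form question. A few candidates would be deferred or lost at screening. The number lost rises with the frequency of use: if use is rare, both the loss and the benefit are small. The sensitivity analysis will have a subgroup size that cannot be known in advance, so it should be read as supportive only.

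**Limit:** the exclusion does not cure any general sham-credibility problem, which would affect patients new to the therapy as well.

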### Interventions

2.4.

#### IM group

2.4.1.

Participants in the observation group will receive infrared moxibustion intervention using an infrared moxibustion chamber (Model CH-6, Hunan Cihui Medical Technology Co., Ltd., Changsha, Hunan). Participants will lie supine with their entire body below the head and neck placed inside the infrared chamber. Infrared moxibustion will be initiated with a single button press. The temperature inside the chamber will be set to 50 °C, with a treatment duration of 40 min, once per day, twice per week, for a total of 8 weeks.

#### Sham IM group

2.4.2.

Participants in the control group will receive sham far-infrared moxibustion intervention. The treatment protocol will be identical to that of the treatment group, except that the device will not emit infrared rays when turned on.

In addition, both groups of participants will receive therapeutic lifestyle changes, including a balanced diet, moderate increase in physical activity, weight control, smoking cessation, and limited alcohol consumption.

